| Abstract | Chronic pelvic pain syndrome (CPPS) has a high incidence and can present with severe symptoms, leading to mental health issues, causing anxiety, depression, and pain catastrophizing, and placing significant stress on families and society. The exact causes and mechanisms of CPPS remain unclear; studies suggest it may be caused by psychological issues and multi-system dysfunction. Therefore, addressing psychological problems is crucial in the treatment of CPPS. Repetitive peripheral magnetic stimulation (rPMS) shows potential effectiveness in treating CPPS, while repetitive transcranial magnetic stimulation (rTMS) has been proven to be effective for anxiety and depression. This study employs a randomized, double-blind method, recruiting 66 CPPS participants with accompanying psychological issues, who are stratified by gender and randomly assigned to three groups (1:1:1): double-target magnetic stimulation group, peripheral magnetic stimulation group, and sham stimulation group, receiving the corresponding treatments. The efficacy and safety of double-target magnetic stimulation in CPPS patients with psychological disorders will be assessed by comparing changes in pelvic pain scores (for females) or the National Institutes of Health Chronic Prostatitis Symptom Index (NIH-CPSI, for males), depression, anxiety, and stress scales (DASS-21), pelvic floor surface electromyography, pudendal nerve motor evoked potentials, and the 36-item Short Form Health Survey (SF-36) scores before and after treatment. | | | | | | | | | | |
| Keywords | | Repetitive Transcranial Magnetic Stimulation, Repetitive Peripheral Magnetic Stimulation, Chronic Pelvic Pain Syndrome, Randomized Controlled Trial | | | | | | | | | |

**三.**Project Team Members (including Principal Investigators)

| Name | Unit | Dgree | Title | Task division | Ethics training | GCP training | Signature |
| --- | --- | --- | --- | --- | --- | --- | --- |
| [name] | Chengdu Anorectal Hospital | Master's degree | Associate Chief Physician | Project Leader | Yes | Yes |  |
| [name] | Chengdu Anorectal Hospital | Doctor | Professor | Project Guidance | Yes | Yes |  |
| [name] | Chengdu University of Traditional Chinese Medicine Affiliated Hospital | Doctor | Chief Physician | Supervision of Project Implementation | Yes | Yes |  |
| [name] | Sichuan Province Fifth People's Hospital | Master's degree | Attending physician | Data organization, statistical analysis | Yes | Yes |  |

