| Treatment plan | (1) Double-target magnetic stimulation group treatment procedure: ① Before treatment: Three checks and seven pairs, conducted by a qualified practitioner for risk assessment, including the patient's mental symptoms, medication treatment effects, and contraindications, etc. ② During treatment: Determine the stimulation plan: individualized stimulation intensity, measure the resting motor threshold during the first treatment.  Rest motor threshold (RMT) determines the magnetic stimulation intensity for the patient, with the rTMS stimulation intensity set at 120% of RMT. Auxiliary positioning devices: based on the positioning cap, the location of the stimulation cortex is determined; for depressed patients, the left DLPFC is selected for 10Hz high-frequency stimulation, while for anxious patients, the right DLPFC is selected for 1Hz low-frequency stimulation. The chair is adjusted to a horizontal position of 10-20°, and the patient lies prone on the chair, with the center of the circular coil aligned with the S3 region. During stimulation, a contraction sensation in the anal sphincter muscles and a plantar flexion response indicate correct positioning. rPMS is performed first, followed by adjusting the chair to a sitting position for rTMS. After the treatment is completed, the patient is asked about any discomfort, and elderly patients are advised to sit by the bedside for a moment before leaving. The doctor completes all types of record forms and keeps them for future reference; the treatment room is disinfected and isolated.  (2) Peripheral magnetic stimulation group: ① Before treatment: same as the double-target magnetic stimulation group. ② During treatment: only rPMS is performed, with the same operation as the double-target magnetic stimulation group. ③ After treatment: same as the double-target magnetic stimulation group.  (3) Sham stimulation group: ① Before treatment: Same as the dual-target magnetic stimulation group. ② During treatment: Use coils that do not generate a magnetic field, only producing sound, first applying sham peripheral magnetic stimulation to the S3 region, followed by sham transcranial magnetic stimulation, with the same procedure as the dual-target magnetic stimulation group. ③ After treatment: Same as the dual-target magnetic stimulation group.  (4) Treatment regimen: A course consists of 20 sessions, with 5 sessions per week, and 1 session each day; patients need to actively inform the therapist when there are significant adjustments to the types and dosages of medications.  (5) Emergency Situation Handling: The system should provide protective measures in accordance with the requirements of GB9706.1-2007, such as an emergency braking device. During the treatment process, if unexpected seizures, loss of consciousness, or other emergencies occur, immediately take the following measures for handling and first aid: ① Immediately stop rTMS treatment; ② Ensure the patient's airway is clear; ③ Closely monitor the patient's vital signs; ④ For cardiac arrest or respiratory failure, immediately perform cardiopulmonary resuscitation; ⑤ Contact the patient's family to inform them of the situation and the corresponding handling measures. After the emergency situation is resolved, summarize the experiences and lessons learned. |

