5.1 Sample Size Estimation

According to the research by Yang Jing-ming and his colleagues, under the conditions of β=0.1 and α=0.05, the effect size is 0.5. Pain scores will be used as the primary measurement standard, and G*Power 3.1.9.7 will be used to estimate the sample size. It is calculated that there will be approximately 54 patients in the study cohort, and considering a 10% dropout rate, each group will include 22 people, requiring a total of 66 participants for this RCT.

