5.2 Patient Number and Randomization Group

Input patient data into the computer to obtain a subject number. All subject numbers will be three digits long, and patients will consistently use this number throughout the study, which will not be reassigned. Patients who withdraw their informed consent or discontinue the study after their patient number has been assigned will retain their initial number. Randomization will be conducted using a stratified block randomization method, stratified by gender, followed by block randomization within each stratum. Since the purpose of this study is to compare the improvement in symptom scores of chronic pelvic pain as well as anxiety and depression scores, gender is an important influencing factor. Therefore, gender will be used as a stratification factor, and block randomization (with 2 blocks per stratum and a block length of 4) will be employed for grouping. The aforementioned stratified block randomization can be implemented using SPSS software.

6. Research steps or treatment plan

6.1 Clinical intervention measures and steps.

(1) Before treatment: Conduct three examinations and seven comparisons. Researchers will carry out a risk assessment.

(2) Stimulation plan: First conduct rPMS, then conduct rTMS.

(3) Stimulation Site: For peripheral stimulation, the center of the circular coil will be aligned with the S3 region. During the stimulation process, if you feel contractions in the perineal muscles and dorsiflexion responses in the feet, it indicates that the position is correct. For central stimulation, the left DLPFC (l-DLPFC) region will be targeted for patients with major depressive disorder, while the right DLPFC (r-DLPFC) region will be targeted for patients with generalized anxiety disorder.

(4) Stimulation intensity: For peripheral stimulation, 50% of the maximum stimulation intensity will be applied. For central stimulation, the setting will be adjusted to 120% of the resting motor threshold (RMT).

(5) Stimulation parameters: ① Peripheral stimulation: 20 Hz, 2 seconds of stimulation, 28 seconds interval, a total of 1600 pulses. ② r-DLPFC: 1 Hz, 10 seconds of stimulation, 2 seconds interval, a total of 1000 pulses. ③ l-DLPFC: 10 Hz, 4 seconds of stimulation, 26 seconds interval, a total of 3000 pulses.

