14.4 Setting up the experimental blind method

A researcher will place the random sequence numbers generated by SPSS software into opaque envelopes separately and number the envelopes in order on the surface. This researcher will not participate in other studies and will ensure that the envelopes containing the random sequence numbers remain sealed throughout the research process, so that other personnel will not know the random sequence numbers inside the sealed envelopes in advance. A second researcher will select eligible patients for the study based on inclusion and exclusion criteria. Patients will be informed of the potential benefits and risks of the study, and if they agree to participate, they will sign an informed consent form. The third researcher will ask patients about their condition, assess their status, assist in filling out the CRF forms, and distribute the envelopes to the patients participating in the study. The fourth researcher will treat patients according to the random sequence numbers in the envelopes given to them and will not participate in other studies. The fifth researcher will evaluate and complete the pelvic pain scale (for women) / National Institutes of Health Chronic Prostatitis Symptom Index (NIH-CPSI) (for men), the DASS-21 scale, and the SF-36 quality of life scale assessments, and will complete the patients' pelvic floor surface electromyography and pudendal nerve motor evoked potential tests. This researcher will not participate in data analysis or other studies. After data collection is completed, the first unblinding will occur, with two researchers entering and verifying the data separately. Finally, a statistical analyst will conduct the statistical analysis, comparing the three groups without knowing the group assignments. After the analysis is completed, a second unblinding will take place, marking the end of the study.

15. Preservation of Data and Records

Researchers are responsible for ensuring that research records are not accidentally damaged; the medical records of subjects should be clearly labeled to prevent accidental destruction of documents due to errors. Researchers and research institutions must retain clinical trial-related materials for five years after the conclusion of the clinical trial. Original medical documents should be kept according to the relevant regulations of the hospital, but must not be less than five years after the conclusion of the clinical trial.

16. Research Process

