**Appendix 7 Table 6 Randomization Application Form**

Application Date: Year Month Day Random Number:

| **General Information** | | | |
| --- | --- | --- | --- |
| Name Abbreviation: | | Age: years | Gender: Male □ Female □ |
| Weight： Kg | | Height： m | BMI Index： Kg/m2 |
| DMS-5 Diagnosis | Generalized Anxiety Disorder Severity: Mild □, Moderate □, Severe □ | | |
|  | Severity of Major Depression: Mild □, Moderate □, Severe □ | | |

| Selection Criteria Checklist | | |
| --- | --- | --- |
| Inclusion criteria | Yes | No |
| 1.Meeting the CPPS diagnostic criteria in the 2022 EAU guidelines | □ | □ |
| 2. Definitive generalized anxiety disorder or major depressive disorder | □ | □ |
| 3. Individuals aged between 18 and 70 years | □ | □ |
| 4.No identifiable pathological changes in physical examinations and auxiliary tests | □ | □ |
| 5.No treatment other than oral medications in the 3 months prior to the visit | □ | □ |
| 6.Patient's informed consent and voluntary participation in the study | □ | □ |
| All of the above criteria must be "yes," otherwise the patient cannot be enrolled. | | |

| Exclusion Criteria Checklist | | |
| --- | --- | --- |
| Exclusion criteria | Yes | No |
| 1. Patients in the acute phase of systemic and intracranial hemorrhagic diseases | □ | □ |
| 2.Individuals with serious underlying conditions, such as cardiovascular, liver, kidney, respiratory, and blood disorders, in addition to malignant tumors and other advancing illnesses | □ | □ |
| 3.Patients with cardiac metal membranes, cardiac pacemakers, intracranial metal implants, lumbar sacral metal implants, and implantable electronic devices | □ | □ |
| 4.Individuals with infections in the head or lumbar sacral regions | □ | □ |
| 5.Individuals exhibiting unstable vital signs | □ | □ |
| 6.Patients with previous adverse reactions to magnetic therapy | □ | □ |
| 7.Individuals with atypical autonomic reflexes | □ | □ |
| 8. Patients with cognitive impairment who cannot cooperate | □ | □ |
| 9. Expectant or breastfeeding women | □ | □ |
| 10. Patients with a history diseases causing peripheral nerve damage | □ | □ |
| 11. Patients with debilitating diseases, such as malignant effusion, active pulmonary tuberculosis, cancer, or myasthenia gravis | □ | □ |
| 12.Patients with severe mental illness or epilepsy | □ | □ |
| All of the above criteria must be "no"; otherwise, the patient cannot be enrolled. | | |

Is it eligible for enrollment: Yes □ No □

Reason for not enrolling:

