Randomization results for eligible participants:

Group A (dual-target magnetic stimulation) □

Group B (peripheral magnetic stimulation) □

Group C (sham stimulation) □

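### Allocation could become partly predictable if past assignments reach enrolling staff: the block length is fixed and printed, and the eligibility form also records the arm

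*Protocol*

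**What the plan says.** Section 5.2 randomises patients "stratified by gender, followed by block randomization within each stratum", and specifies that "block randomization (with 2 blocks per stratum and a block length of 4) will be employed for grouping". The abstract gives three arms at 1:1:1, and section 5.1 ends with "requiring a total of 66 participants for this RCT".

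Section 14.4 sets out concealment. One researcher generates the sequence and seals it in opaque, numbered envelopes, and other staff are not to know the contents beforehand. Enrolment belongs to someone else: "A second researcher will select eligible patients for the study based on inclusion and exclusion criteria". A third researcher hands out the envelopes, a fourth treats according to them, and a fifth assesses outcomes.

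Appendix 7 (Table 6) is one form. It records sex, a random number and the eligibility checklists, then the decision line "Is it eligible for enrollment: Yes □ No". It closes with a part headed "Randomization results for eligible participants", with a box for each arm and the treatment spelled out beside it. The protocol does not say who completes that last part, who keeps the form, or who may see it afterwards.

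For the peripheral arm, the treatment plan in the Plan Summary says "only rPMS is performed, with the same operation as the double-target magnetic stimulation group". The sham arm has both a sham sacral and a sham head procedure.

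**The concern.** Sealed envelopes hide the next assignment only as long as it cannot be worked out from earlier ones. With a fixed, published block length, anyone who knows the earlier arms in the current block of a sex stratum knows something about what is left, and sometimes knows the next arm for certain.

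The plan leaves two routes by which past arms could become known. The first is the Appendix 7 form, which puts the eligibility decision and the named arm on the same document. The second is the treatment itself: all patients are treated at one hospital's pelvic floor centre, and a patient who never has a head procedure is evidently in the peripheral arm.

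What is at stake is selection at recruitment. Eligibility includes matters of judgement, such as the absence of significant pathological change. Someone who can guess the next arm could enrol, defer or decline a patient accordingly. The primary outcome is a patient-reported symptom score. A prognostic imbalance that arose from unrecorded clinical impressions could be reduced by baseline adjustment but not reliably removed.

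**Working it through.** **Inputs.** Two sex strata, two blocks per stratum, block length 4 (section 5.2); three arms at 1:1:1 (abstract); 66 patients (section 5.1).

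**The printed scheme.** It yields 2 × 2 × 4 = 16 assignments, against 66 needed (66/4 = 16.5 blocks). Four is not a multiple of three, so a block of 4 cannot be balanced across three arms. That is a separate error. It matters here because no predictability figure follows from the scheme as printed, so lengths have to be assumed. I take balanced blocks of 3 and 6, and a block of 4 holding each arm once plus one extra slot drawn at random and unknown to the guesser.

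**Method.** Enumerate every equally likely block. At each position, guess the arm most likely to come next given what has been seen in that block. Average the chance of being right over positions. With nothing seen, the chance is 1/3 = 33.3% for all three lengths.

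**All past arms in the block known:**

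- Block of 3: (1/3 + 1/2 + 1)/3 = 61.1% correct. The last of three is always certain, so 33.3% of assignments are certain.
- Block of 6: (1/3 + 2/5 + 1/2 + 8/15 + 3/5 + 1)/6 = 56.1% correct; (1/5 + 1)/6 = 20.0% certain.
- Block of 4, unknown extra slot: (1/3 + 5/12 + 7/12 + 2/3)/4 = 50.0% correct; (1/2)/4 = 12.5% certain.

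**Only peripheral patients recognised, form never seen:**

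- Block of 3: (1/3 + 1/2 + 2/3)/3 = 50.0%.
- Block of 6: (1/3 + 2/5 + 13/30 + 13/30 + 8/15 + 2/3)/6 = 46.7%.
- Block of 4, unknown extra slot: (1/3 + 5/12 + 17/36 + 1/2)/4 = 43.1%.

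In this second case dual and sham patients look alike to the observer. The guess therefore has the same distribution before a dual patient as before a sham patient, and the expected dual-minus-sham difference in guesses is exactly zero. Only comparisons with the peripheral arm could be affected.

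**Does varying the length help?** A simulation with 33 patients per sex (an assumed even split of 66) and all past arms visible gives 54.8% correct for a fixed block of 6 and 53.6% for lengths varied between 6 and 9. The gain is about one percentage point. Keeping past arms hidden returns guessing to 33.3% for any balanced length.

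**The case against.** The strongest reply is that section 14.4 is written to prevent this. Envelopes are opaque, sealed and numbered. The person who selects patients neither holds the list, distributes the envelopes nor gives the treatment. Selection comes before the envelope is handed over, so the arm boxes in Appendix 7 must be filled in later, and nothing says that the second researcher does so or sees the result. Nor does any text place that researcher at treatment sessions. Section 10.1.1 mentions clinical experience only for a preliminary judgement, and formal confirmation against the criteria follows.

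Most of this stands. A reader might infer that enrolling staff can predict the next assignment. The documents do not support that: prediction needs knowledge of past arms, and no passage gives it to them. What remains is that section 14.4 speaks only of not knowing the sequence in advance. It is silent on past arms and on the Appendix 7 result part.

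A reader might also infer a higher rate for the block of 4. If the extra slot were known to belong always to one arm (2:1:1), full knowledge of the past would give 64.6% correct. The protocol states 1:1:1 and mentions no such rule. Under it, naming the doubled arm every time would already be right in 50% of cases with nothing leaked, so 33% would not be the baseline.

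**Conclusion.** The point holds as a conditional weakness in concealment. The fixed printed length, the combined form and the recognisable peripheral arm are all in the protocol. Whether past arms reach enrolling staff is left open.

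If all past arms in the stratum were known, correct guesses would rise from 33% to about 61%, 56% or 50% (fixed 3, fixed 6, or 4 with an unknown extra slot). If only peripheral patients were recognised, they would rise to about 43% to 50%, with no dual-versus-sham bias from that route. These figures rest on the assumed block structures and on optimal guessing, so they are upper limits for each case.

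A reader might go on to put a bias in standard deviations on the treatment effect. That would need the amount by which recruiters shift prognosis when they act on a guess, and how often they act. The documents give neither, so the size of any bias cannot be derived.

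The point still deserves action now. Section 5.2 has to be rewritten anyway because 4 does not fit three arms, and replacing it with a fixed, printed 3 or 6 would leave this weakness in place.

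**What to change.** 1. Remove the result part from the Appendix 7 enrolment form. Record the arm on a separate record seen only by the list holder (first researcher) and the treating researcher (fourth), and say so in section 14.4 so that the two places agree. This is the change that does most of the work.
2. As a secondary measure, when section 5.2 is rewritten, use randomly varied block lengths in multiples of 3 within each sex. Keep the lengths in a restricted document away from enrolling staff. The calculated gain is small if past arms are visible, so this does not replace the first change.

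The cost is one extra form, an edit to sections 5.2 and 14.4, and slightly more possible imbalance within a sex stratum if the last block is incomplete. Envelopes, software and the five researcher roles stay as they are. The form change does not stop peripheral patients being recognised by anyone who sees the sessions. That route remains, at the lower rates shown above.

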10.4 Expected Number of Recruits

66 patients with chronic pelvic pain syndrome accompanied by mental and psychological disorders who meet the selection criteria.

10.5 Time of participation in the study (duration of each participation and total time)

Participants who have been enrolled and received the first week of treatment (5 sessions) are considered to have participated in the study for the first time; participants receive 5 treatments per week for a total of 4 weeks (20 sessions); after the treatment course ends, they return to the hospital 8 weeks later for further examinations and assessments; the total duration of participation in the study ends 8 weeks after the treatment course concludes.

11. Data Management and Statistical Analysis Plan

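### Two blocks of 4 per sex (Section 5.2) cannot deliver a balanced 1:1:1 allocation of 66 patients to three arms

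*Protocol*

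**What the plan says.** The abstract in the application form describes patients "stratified by gender and randomly assigned to three groups (1:1:1"). Section 5.1 sets the size: "each group will include 22 people, requiring a total of 66 participants for this RCT". Section 10.4 repeats the total, and the randomisation form in Appendix 7 lists three groups, A, B and C.

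Section 5.2 fixes the method. Allocation is "stratified by gender, followed by block randomization within each stratum", and the block structure is "block randomization (with 2 blocks per stratum and a block length of 4) will be employed for grouping". Sex is the only stratification factor, and SPSS is named as the tool.

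Section 14.4 describes how the sequence is put into numbered, opaque, sealed envelopes and which researcher does what. It gives no other block length, no further blocks and no rule for extending the list. Neither does any other part of the protocol.

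**The concern.** A permuted block guarantees the allocation ratio only if its length is a multiple of the sum of the ratio, which is 3 here. A length of 4 is not. Separately, the stated number of blocks has to supply an assignment for every patient, and two blocks of 4 per sex supply far fewer than 66.

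The consequence is practical. The person who builds the list has to choose a block length, a number of blocks and an arm for the surplus place, and none of these choices is in the protocol. The list then cannot be checked against the text that was approved.

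Balance within sex matters more than usual in this trial. Section 8.1 measures the primary outcome with a different instrument in each sex: the pelvic pain scale in women and the NIH-CPSI in men. If the arms differ in sex mix, they also differ in the mix of instruments behind the primary result. Section 5.2 itself gives the influence of sex as its reason for stratifying.

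**Working it through.** **Inputs**

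| Quantity | Value | Source |
|---|---|---|
| Arms and ratio | 3, 1:1:1 | Application form abstract; Appendix 7 |
| Total and per arm | 66; 22 | Section 5.1 |
| Strata | 2 (sex) | Section 5.2 |
| Blocks per stratum | 2 | Section 5.2 |
| Block length | 4 | Section 5.2 |

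**1. The plan's own totals.** 3 × 22 = 66, so ratio, arm size and total agree with one another. The conflict is with the block scheme.

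**2. Block length against the ratio.** 4 = 3 × 1 + 1, so each block has one place left over and the closest composition is 2:1:1. Two blocks give a stratum 2 × 4 = 8 places, and 8 = 3 × 2 + 2, so the stratum total is not divisible by three either.

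**3. Number of assignments.** Strata × blocks × length = 2 × 2 × 4 = 16. Shortfall: 66 − 16 = 50 patients, and 50/66 = 76%.

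**4. Other readings of the text**

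- Drop the two-block limit and keep length 4: 66/4 = 16.5 blocks, each full one still unequal.
- Take 4 as places per arm, so length 12: 2 × 2 × 12 = 48, still below 66.
- Keep two blocks per stratum and solve for length: 66/(2 × 2) = 16.5, not a whole number.

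None restores agreement with both the ratio and the total. The shortfall also does not depend on how the total was reached. Against the 54 that Section 5.1 gives before dropout, 16 is still 38 short.

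**5. Size of the imbalance if unequal blocks of 4 were used anyway.** Suppose there are about 16 blocks and the surplus place goes to each arm with probability 1/3.

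- Each arm averages about 22, with SD √(16 × 1/3 × 2/3) = √3.56 ≈ 1.9.
- The variance of a difference between two arms is proportional to 1/n₁ + 1/n₂. For 24 against 20 this is 1/24 + 1/20 = 0.0917. For 22 against 22 it is 2/22 = 0.0909. The loss is under 1%.
- If the surplus rotated, the arms would be level after every third block (12 patients, 4 per arm) and not in between.
- Extreme case, the same arm taking every surplus: 66 × 2/4 = 33 and 66 × 1/4 = 16.5 in each of the others. The large arm against a small one gives 1/33 + 1/16.5 = 0.0909, the same as the balanced design. The two small arms against each other give 2/16.5 = 0.121, a third more variance.

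**6. What a multiple of 3 gives.** With length 6 (two places per arm), two arms within a sex can never differ by more than 2; with length 3, by more than 1. The protocol states no sex split, so the number of blocks is shown for assumed splits:

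| Assumed split | Blocks of 6 needed |
|---|---|
| 33 / 33 | 6 and 6 |
| 22 / 44 | 4 and 8 |
| 11 / 55 | 2 and 10 |

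A list of 66 entries per sex (66/6 = 11 blocks of 6, or 66/3 = 22 blocks of 3) covers every split.

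**The case against.** The strongest reply is that little is lost in practice. Software can generate a list from unequal blocks of 4, and step 5 shows that a random or rotating surplus would leave the arms close to 22 each, with almost no loss of precision. That stands, and it limits the point. A reader might infer that no list can be produced at all. The text does not support that: what cannot be produced is the balanced scheme for 66 patients that the protocol states.

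A reader might also infer that the trial will end up allocated 2:1:1, about 33:16.5:16.5. That requires the same arm to take the surplus in every block, and nothing in the protocol says so.

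A third inference is that a fixed block length lets the treating researcher guess coming assignments, so that allocation is compromised. Section 14.4 weighs against this. One researcher selects patients, another hands out the envelopes, another treats and another assesses, and the envelopes are opaque, numbered and sealed. The person who sees the assignments does not decide who enters. Avoiding a single disclosed block length is good general practice, but its absence is not shown to cause harm here.

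Finally, the count of 16 depends on taking the two-block limit literally in a text whose English is often awkward. It is the less certain of the two arithmetic points. The mismatch between a length of 4 and three arms does not depend on that reading.

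**Conclusion.** The point holds as a contradiction within the protocol. The block length of 4 conflicts with 1:1:1 allocation to three arms, and the stated number of blocks, read literally, covers 16 of 66 patients. The scheme as written cannot deliver the stated balanced allocation, and exact balance within each sex is not secured.

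The likely statistical cost of an improvised list is small if the surplus place rotates or is random, which is an assumption because the protocol is silent on it. The firmer harm is that the list builder must depart from the protocol and the resulting list cannot be audited against it. This is not a detail that could be left to another document: Section 5.2 states the block structure, and states it in a form that conflicts with the ratio and the total. It should be corrected because randomisation underlies every between-group comparison and the repair is cheap. The protocol does not show which list was actually generated, so no conclusion is drawn about how patients have been allocated.

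**What to change.** Replace the block wording in Section 5.2 with text such as:

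> Permuted blocks whose length is a multiple of 3, allocation 1:1:1, generated separately for men and women, with enough blocks in each stratum to cover any sex split of the 66 patients.

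Preferably hold the actual block sizes (for example, randomly varying 3 and 6) in a restricted randomisation document and not in the protocol, which recruiting and treating staff use. Any multiple of 3 cures the arithmetic; varying the sizes is a sensible addition, not a necessity.

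Section 10.2 plans recruitment from January 1, 2024. If it has begun, document the list actually used, including block lengths and the handling of any surplus place, and correct it going forward.

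Cost: one paragraph of protocol text, a regenerated list and new envelopes. No extra patients are needed.
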